### 7. Statistics and sample size justification

Sample size considerations focus on the primary hypothesis posited in the Specific Aims section. The major research goal is to determine the efficacy of having patients use the asthma module of the interactive website, for a period of 12 months, for improving asthma control. The primary outcome will be asthma control, based on the Asthma Control Test (ACT), a valid and reliable 5-question self-report measure of asthma control. 98-100. We chose to power the study based on asthma control, as it is a powerful predictor of emergency department visits, activity limitations and missing days of work due to asthma 6,100,130, and it is a central goal in both Healthy People 2010 as well as in the 2007 NAEPP Guidelines 26,131. We chose not to power the study on improving the use of controller medications, such as inhaled corticosteroid use, as the rates of use of these medications has increased greatly over the past decade, which would lead to a ceiling effect 7. Despite the broad use of these controller medications, however, asthma control rates are still in the 50% range, so we will not suffer from such a ceiling effect 5. Our estimated baseline rate of 55% is based on two studies of asthma control in similar groups of insured patients that both showed asthma control rates in the 50% range 5,6. For example, Schatz and colleagues observed that 48.4% of 570 insured adults with asthma had an Asthma Control Test (ACT) score of less than 20, the same measure of asthma control that we are using in the current study 5. Vollmer and colleagues reported that 48% of 5,181 insured adults with asthma reported good asthma control, using a slightly different measure of asthma control, the Asthma Quality of Life Questionnaire 6. We expect a slightly higher baseline control rate, as patients who volunteer for clinical trials tend to be healthier than those who do not 132. This expected effect size is based on a meta-analysis by Stone and colleagues that examined the efficacy of reminders, given to patients, on rates of adult immunization and cancer screening services 16. Patient reminders, similar to what we plan to use in the current study, significantly increased immunizations (odds ratio, OR=2.5), mammography utilization (OR=2.3), cervical cytology screening (OR=1.7) and colon cancer screening (OR=2.8). These effect sizes are consistent with reviews by other investigators 23,50,133. In the current study, we will be powered to detect an effect size that translates to a relative risk of 1.3 (0.70 /0.55) and odds ratio of 1.9. We chose this conservative effect size to address the fact that we are not examining a process of care but an outcome of care. While we expect the intervention to lead to increases in the number of controller medications used, additional medications do not always help patients. Also, we need to be sensitive to the possible differences in efficacy between interventions to increase adult preventive services (e.g., pap testing) and studies such as ours that seek to change chronic disease management practices. We considered powering on a numerical change in the Asthma Control Test (ACT), our main outcome measure, but chose not to do this as there is less consensus about what represents a meaningful change in the ACT than there is about what represents appropriate asthma control 5,98. We will, however, analyze changes in the ACT as a continuous variable, in our secondary analyses. Formulas based on the chi-square test were used to derive sample size calculations from the following assumptions. We assume a type I error rate (alpha) of 5% (0.05), 80% (0.80) power, and a two-tailed test, which allows us to detect significant differences in either direction. We expect a 12-month retention rate of 80%, although we believe that our procedures will substantially minimize the likelihood of attrition. We considered randomizing providers but felt that, given the number of providers in the two geographical areas, it was very unlikely that a physician would have more than one subject enrolled in the study. We will, however, track the name of the asthma care provider, so that we can include this variable in a sensitivity analysis, to be certain that adding this variable does not change the conclusions of the data analyses. In order to achieve 80% power to detect a difference of 70% vs. 55% between intervention and control group, we will need to randomize 408 patients into the two conditions at baseline. This assumes that no more than 20% are lost to follow-up at 12 months, leaving no fewer than 326 subjects available for analysis at the end of the study. We do concede, however, that smaller differences in asthma control may be clinically important, particularly on a population level. To power the study on a 10% difference in asthma control, however, we would have needed to recruit 940 subjects, which we felt would unnecessarily increase the cost and complexity of the study.

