
Preliminary data analysis plan: All analyses will be conducted using SAS Version 9. Initially, descriptive statistics such as the minimum, maximum, range, median, quartiles, mean, and standard deviation for each continuous variable and frequencies and percentages for each categorical variable will be used to summarize all variables as well as detect outliers, data entry mistakes, and missing values. These descriptives will be used to “clean” the data prior to analysis. Exploratory graphical techniques will be used to further examine these data. The normality of the distribution of mediators of interest, both in their original and transformed state (if necessary), will be examined with a normal probability plot when applicable. Longitudinal plots will be used to identify trends over time that are both population- and individually-based.

Differential dropout and attrition: Initially, the two randomized groups will be compared on important demographic and other baseline variables to ensure successful randomization. If it is determined that the groups, by chance, are significantly different on some measures, we will include those theoretically meaningful confounders as covariates in subsequent analyses. T-tests, ANOVA, and/or chi-square tests of independence comparing those who complete the study with those lost to follow-up will be performed on baseline demographic variables, asthma control, asthma-related quality of life, and baseline use of controller medications to identify potential differential dropout. These comparisons ensure equality of intervention and comparison groups after accounting for study attrition. For the primary outcome, we will apply intention to treat (ITT) principles with all available data included in the first set of analyses 134. Second, subjects lost to follow-up will be conservatively assumed to have not changed their level of asthma control between baseline and 12 months. Similar findings between both approaches would increase confidence in the results overall.

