Missing data: For exploratory analyses, if the combined rate of missingness on predictor variables is less than 5%, the missing data will not be replaced. In the event of unanticipated higher levels of missing data, we need to examine the nature of the missing values. If it is believed that variations in attrition can be explained by observed variables (e.g. if those who are observed to have poorer asthma control at baseline are more likely to drop out), this corresponds to the missing at random (MAR) assumption and the models as we have specified them will give valid inferences because they are likelihood-based 135, and no special adjustments are necessary. If instead we believe that some of the variability in attrition might further be explained by variables not observed, then we will employ multiple imputation 136 (i.e., using PROC MI in SAS) which have been shown to yield estimates that are comparable to those that would be obtained if the data were all present. Because such imputations are necessarily based on assumptions that cannot be verified, we will carry out sensitivity analyses to investigate violations of these assumptions.

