Analysis of main outcome: Data analysis will focus on the primary hypotheses that significantly more subjects in the IC will have their asthma controlled, an Asthma Control Test (ACT) score of ≥ 20, than subjects in the CC. This dichotomized version of the ACT at 12 months is the primary outcome. We considered powering on a numerical change in the Asthma Control Test (ACT), our main outcome measure, but chose not to do this as there is less consensus about what represents a meaningful change in the ACT than there is about what represents appropriate asthma control 5,98. Logistic regression will be used to analyze asthma control at 12 months. Logistic regression allows for inclusion of the two dichotomous strata. Also, it is possible that the groups may have differences at baseline in potential confounders (e.g. socio-economic status, asthma symptoms) that may contribute to group differences in the 12 month event rate between the two conditions. Logistic regression permits inclusion of these potential confounders as covariates. Additionally, as the ACT is measured every 3 months, the logistic regression model can be extended using the generalized estimating equations (GEE) approach of Zeger and Liang (1986) with a logit link so that the repeated measures on each subject can be included in the analyses 137. Thus, asthma control can be examined at any of the preceding time points as well. Tests of the primary hypotheses about intervention effects will be formulated directly in terms of the main effect of intervention. We will also assign a create variables for physicians’ practices, so that physicians who practice together will be given the same variable number. In our analyses we first perform intent-to-treat (ITT) analyses and then will perform analysis including physician- and practice-level variables, while accounting for clustering.

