**Figure 2: Computer Network**

Subjects will be told to skip any items on the questionnaire that they would prefer not to answer, which will reduce the likelihood of psychological stress induced by the questionnaires. Every effort will be made to verify that the feedback given to subjects is accurate. To do this we will 1) work with [name] to rewrite the feedback to ensure that it is up to date with consensus treatment recommendations, 2) have the feedback reviewed by a primary care provider ([name]) and 3) perform extensive software testing, given a range of test cases. Also, as the recommendations in the feedback require a physician to implement, the participating primary care physicians will form an additional layer of quality control by implementing recommendations from the reports that they deem to be appropriate for the specific patient.

At the end of the study, Penn State researchers will provide Highmark with a list of participant names, DOB’s, gender, and date they agreed to the member authorization form. This list will be sent through a secure Highmark server and only those we are working in collaboration with on the asthma project will have access to this list in order to pull claims data on these participants. The claims data information will then be sent through a secure server to Penn State in order to minimize the risk of breach of confidentiality.

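### The missing-data paragraph uses an attrition argument to justify making no adjustment when predictors are missing at random above 5%; that argument covers neither missing predictors nor the planned GEE models

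*Protocol*

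**What the plan says.** All references are to the Protocol. In section 7, the Missing data paragraph has three parts.

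- **Below 5%.** In a sentence that limits itself to exploratory analyses, "if the combined rate of missingness on predictor variables is less than 5%, the missing data will not be replaced".
- **Above 5%, MAR.** If attrition can be explained by observed variables, "the models as we have specified them will give valid inferences because they are likelihood-based 135, and no special adjustments are necessary".
- **Above 5%, otherwise.** If unobserved variables are thought to explain some of the attrition, multiple imputation with PROC MI is used, with sensitivity analyses on its assumptions.

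Other text decides where this matters:

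- Differential dropout and attrition (section 7) applies intention to treat to the primary outcome "with all available data included in the first set of analyses". It also brings baseline variables that differ significantly by chance, and are theoretically meaningful, into later models.
- Analysis of main outcome (section 7) notes that "Logistic regression permits inclusion of these potential confounders as covariates", with socio-economic status and asthma symptoms as examples, and offers a GEE extension for repeated ACT measures. Secondary analyses uses GEE for dichotomous outcomes and linear mixed models for continuous ones.
- Analyses of mediating and moderating processes (section 7) plans treatment-by-covariate interactions. Section 6 lists education and household income among the moderators.
- Safeguards and Confidentiality, below Figure 2: "Subjects will be told to skip any items on the questionnaire that they would prefer not to answer".

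**The concern.** The paragraph begins with one problem, blank predictors, and answers a different one, subjects who drop out. The answer does not transfer. A regression conditions on its predictors, so a subject with a blank covariate cannot enter the fit unless the value is filled in or modelled. If the value is neither replaced nor adjusted for, the usual SAS regression procedures omit that subject, even when the 12-month ACT was recorded.

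At stake are the precision and comparability of the adjusted and moderator results. An adjusted estimate would rest on a smaller, different sample from the unadjusted one, so a shift between them could reflect either the adjustment or the change of sample. Blanks are foreseeable, because subjects are told they may skip items and some planned moderators are sensitive self-reports.

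**Working it through.** **1. Does the stated reason cover the stated problem?**

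| Model planned in section 7 | Likelihood-based? | Outcome missing, MAR | Predictor missing, MAR |
|---|---|---|---|
| Logistic regression at 12 months | Yes | Covered, given the covariates in the model | Not covered; row dropped |
| Linear mixed model | Yes | Covered | Not covered; row dropped |
| GEE with logit link | No | Not covered by this argument | Not covered; row dropped |

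The exemption is sound for missing outcomes in the first two rows only. The imputation branch does not close the gap. It applies when unobserved variables are suspected, whereas standard multiple imputation itself assumes MAR. Predictors missing at random above 5%, the case imputation suits, fall under the branch that does nothing.

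**2. Reproduce the plan's sample size.** The inputs, all from section 7, are "We assume a type I error rate (alpha) of 5% (0.05), 80% (0.80) power, and a two-tailed test"; the aim "to detect a difference of 70% vs. 55% between intervention and control group"; 20% loss; and "we will need to randomize 408 patients into the two conditions at baseline", leaving 326 for analysis. Equal allocation is assumed, since the ratio is not stated.

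n per arm = [z(0.975)·√(2·p̄·(1−p̄)) + z(0.80)·√(p₁(1−p₁) + p₂(1−p₂))]² / (p₁−p₂)², with p̄ = 0.625

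- First term: 1.960 × √0.46875 = 1.342
- Second term: 0.842 × √(0.21 + 0.2475) = 0.842 × 0.6764 = 0.569
- n = (1.911)² / 0.15² = 162.3, rounded up to 163 per arm, 326 in total
- 326 / 0.80 = 407.5, rounded up to 408

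Both figures reproduce. Neither contains an allowance for subjects lost to blank covariates.

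**3. Power if a share m of the 326 is dropped.** With n = 163(1−m) per arm:

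power = Φ[(0.15·√n − 1.342) / 0.6764]

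| Blank on a model covariate | Subjects left | Lost | Power |
|---|---|---|---|
| 0% | 326 | 0 | 80.2% |
| 5% (the plan's threshold) | 310 | 16 | 78.1% |
| 10% (assumed) | 293 | 33 | 75.9% |
| 15% (assumed) | 277 | 49 | 73.5% |
| 20% (assumed) | 261 | 65 | 70.8% |

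For the 5% row: n = 154.85, and (0.15 × 12.444 − 1.342) / 0.6764 = 0.776, so Φ = 0.781. The percentage is the share of subjects with at least one blank among the model's predictors. The protocol gives no expected rate, so everything above 5% is an assumption.

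**4. Bias or precision?** A simulation used 326 subjects and 1,500 runs per setting, with a treatment log odds ratio of 0.69 and an assumed covariate log odds ratio of 0.8. Blanks were either completely random or dependent on the covariate's own value. Each cell gives the mean treatment log odds ratio and the power.

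| Nominal blanks | Full data | Complete cases | Mean fill plus missing indicator |
|---|---|---|---|
| 5%, random | 0.706; 81.5% | 0.710; 80.1% | 0.704; 81.3% |
| 5%, by value | 0.707; 81.5% | 0.711; 77.7% | 0.703; 80.9% |
| 15%, random | 0.691; 80.1% | 0.691; 72.9% | 0.680; 79.9% |
| 15%, by value | 0.701; 80.5% | 0.702; 70.9% | 0.685; 79.6% |

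Dropping subjects left the treatment effect essentially unbiased and cost power. Simple filling recovered nearly all of that power. Blanks did not depend on arm, or on the outcome beyond the covariate, so other mechanisms are untested.

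**The case against.** The strongest reply is that the plan says less than a critic may read into it. Much of this stands.

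- **Scope.** The 5% rule is for exploratory analyses. A reader might infer that it governs the primary comparison; no text says so. The primary outcome has its own rule, which includes all observed outcomes first and then assumes no change in subjects lost to follow-up.
- **Not every gap loses subjects.** A reader might infer that any skipped covariate deletes people. The imputation branch, with its sensitivity analyses, rules that out.
- **The 80% power is not undermined.** It was derived with chi-square formulas for the two-group comparison and is not claimed for an adjusted model. Covariates enter only if a meaningful baseline variable differs significantly between arms, and that variable must also have blanks. Age, gender, race and ethnicity come from the phone screener, so they are less exposed to skipping online.
- **Deletion is inferred.** The protocol does not state it. It follows from leaving values unreplaced and unadjusted, together with ordinary software behaviour.
- **The all-available-data commitment** is set against loss to follow-up, so it concerns outcomes rather than covariates.
- **The exemption mentions attrition, and a separate analysis plan could add detail.** This stands only in part. The sentence continues a paragraph about predictors, offers itself as the answer to higher missingness there, and speaks of the models as specified, which include GEE. An incorrect justification written into the protocol is not a detail left for later.

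**Conclusion.** The concern holds in a limited form. The protocol justifies making no adjustment above 5% predictor missingness with an argument that is valid only for outcomes missing at random in likelihood-based models. It leaves predictors missing at random without a remedy and wrongly counts GEE among the likelihood-based models.

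The consequence is confined to moderator models and to any covariate-adjusted treatment effect. Its size for an adjusted comparison is about 2 points of power at 5% blanks (80.2% to 78.1%), and about 4 to 9 points at 10% to 20% (75.9% to 70.8%). These figures assume equal allocation, 326 observed outcomes, the planned 70% against 55%, and rows with blanks being dropped. The range above 5% is illustrative. The figures describe a two-group comparison on the reduced sample and are not power for interaction tests.

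Neither bias in the treatment effect nor a loss of power in the unadjusted primary analysis is shown. The point merits a correction to the text and does not threaten the primary result.

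**What to change.** Revise the Missing data paragraph of section 7 in three places.

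1. Limit the statement that no adjustment is needed to missing outcomes in the likelihood-based models (logistic regression given its covariates, and the linear mixed models). GEE then falls outside it.
2. Add: in any covariate-adjusted estimate of the treatment effect, no subject with an observed outcome is dropped for a missing baseline covariate; missing values are filled from baseline data pooled over arms, without using the outcome, by the mean for continuous covariates and a separate category for categorical ones such as income.
3. For moderator models, where the covariate is itself the question, allow multiple imputation under MAR when predictor missingness exceeds 5%, rather than only when unobserved causes are suspected.

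The cost is a few sentences and a few lines of code, with no new data. Filling slightly distorts the covariate's own coefficient, which matters little for the randomised comparison. In the simulation it also lowered the treatment log odds ratio by 0.011 to 0.016 at a nominal 15% blanks (0.691 to 0.680, and 0.701 to 0.685), a small price for keeping power near 80%. Leaving values unreplaced below 5% in exploratory models is tolerable and can stay.

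### The missing-data rules do not hold for the binary outcomes: the likelihood argument does not cover GEE or assure the 12-month logistic model, and standard multiple imputation is assigned to dropout it cannot address

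*Protocol*

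**What the plan says.** All places are in the Protocol, section 7 (Statistics and sample size justification).

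- **Missing data, MAR case.** The example given is "if those who are observed to have poorer asthma control at baseline are more likely to drop out". In that case "the models as we have specified them will give valid inferences because they are likelihood-based", and "no special adjustments are necessary".
- **Missing data, other case.** If "some of the variability in attrition might further be explained by variables not observed, then we will employ multiple imputation". PROC MI is named, with the assurance that its estimates are comparable to those from complete data. The paragraph closes by promising sensitivity analyses for violated imputation assumptions and names none.
- **Analysis of main outcome.** 12-month control (ACT of 20 or more) is analysed by logistic regression, which "can be extended using the generalized estimating equations (GEE) approach" to use the repeated measures.
- **Secondary analyses.** Binary outcomes use GEE with a logit link; continuous outcomes use a linear mixed-effects model.
- **Differential dropout and attrition.** Baseline covariates enter if the arms turn out significantly different. The primary outcome is analysed first on the available data. In a second analysis "subjects lost to follow-up will be conservatively assumed to have not changed their level of asthma control between baseline and 12 months".

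**The concern.** The MAR rule rests on a property that the binary-outcome models lack or do not exploit. Likelihood inference ignores MAR dropout safely when the likelihood includes the observed data that predict dropout. GEE solves estimating equations and has no likelihood. The 12-month logistic model is fitted by maximum likelihood, but only to subjects with a 12-month ACT and without their 6-month ACT. It is safe only if dropout depends on nothing beyond arm and the covariates in the model, and the covariate rule is triggered by baseline imbalance, not by prediction of dropout.

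The second rule sends the case that the protocol itself contrasts with MAR to a method that assumes MAR. If the unobserved variables also bear on the outcome, standard imputation does not remove the bias and the assurance about complete data fails.

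At stake is the primary comparison. The protocol allows for 20% attrition, and the ACT is completed on the same website that delivers the intervention.

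**Working it through.** **1. The plan's own figure.** Inputs: 55% vs 70%, two-sided alpha 0.05, power 0.80, 20% loss. With mean proportion 0.625, n per arm = [1.960·√(2·0.625·0.375) + 0.842·√(0.55·0.45 + 0.70·0.30)]² / 0.15² = 162.3, so 163 per arm and 326 in total. 326 / 0.80 = 407.5, so 408. Both stated figures reproduce. The planned odds ratio is (0.70/0.30)/(0.55/0.45) = 1.91.

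**2. Which models the likelihood statement covers.**

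| Outcome | Planned model | Statement holds under MAR? |
|---|---|---|
| Primary, binary | 12-month logistic | Only if all predictors of dropout are in the model |
| Primary, repeated (optional) | GEE | No |
| Secondary, binary | GEE | No |
| Secondary, continuous | Linear mixed model | Yes |

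**3. Size, by large-sample simulation.** From the protocol: 70% vs 55% at 12 months, 20% overall dropout, ACT at baseline, 6 and 12 months. (The main-outcome paragraph speaks of ACT every 3 months; the outcome section and the schedule do not.) Assumed, not in the protocol: 55% controlled at baseline in both arms; 6-month control 65% vs 55%; latent correlation 0.6 between visits; log-odds of dropout 1.5 higher if uncontrolled. Imputation is its large-sample form, the observed mean within arm and observed history. GEE was run on 15,000 subjects whose complete-data odds ratio is 1.94, and its working correlation is not stated in the protocol, so two are shown. Odds ratios, truth 1.91:

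| Dropout depends on | Completer logistic, unadjusted | GEE independence | GEE exchangeable | Imputation, baseline + 6 months | No-change |
|---|---|---|---|---|---|
| Baseline control, intervention arm only (MAR) | 2.25 | 2.26 | 1.91 | 1.90 | 1.31 |
| 6-month control, intervention arm only (MAR) | 2.25 | 2.30 | 1.97 | 1.90 | 1.59 |
| 12-month control, intervention arm only (not MAR) | 2.93 | 2.97 | 2.69 | 2.68 | 1.90 |
| Baseline control, both arms | 1.92 | 1.89 | 1.89 | 1.90 | 1.62 |
| 6-month control, both arms | 1.91 | 1.94 | 1.96 | 1.90 | 1.65 |
| 12-month control, both arms | 1.91 | 2.00 | 2.02 | 1.92 | 1.67 |

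Row 1 by hand: completers 73.4% vs 55.0%, so (0.734/0.266)/(0.550/0.450) = 2.26 (2.25 unrounded).

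Adjusting the completer logistic for baseline control changes the target to a conditional odds ratio, 2.16 in the full data. It is recovered in row 1 (2.16) but not in row 2 (2.43), where dropout follows 6-month control.

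**4. Direction of the no-change rule.** In the table it understates the effect in five rows and is close in one. It can also err the other way. Suppose no treatment effect, both arms rising from 45% to 55% regardless of dropout, and losses of 10% (intervention) and 30% (control), all assumed. The rule gives 0.90·55 + 0.10·45 = 54% against 0.70·55 + 0.30·45 = 52%, a false 2-point benefit.

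**The case against.** Several points on the other side stand.

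- Logistic regression and the linear mixed model are both likelihood methods. In the protocol's own MAR example, a baseline-adjusted logistic model is unbiased for its conditional odds ratio, and exchangeable GEE was near the truth. But the protocol does not commit to either: adjustment depends on baseline imbalance and no working correlation is fixed.
- Sensitivity analyses are promised, and their detail may properly sit in an SAP that is not shown. The lack of detail is therefore not the finding. The finding is that plain imputation is named, with an assurance, for the case it does not address.
- The missing-data paragraph opens with exploratory analyses and missing predictors. Its MAR and imputation sentences, however, concern attrition and the specified models, which takes in the outcome analyses.
- The arms differ only in website content, and the active control was chosen to limit attrition. Nothing in the protocol shows that dropout would work differently by arm.

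A reader might infer that the two rules are simply swapped, or that the plan handles no missing data correctly. Neither follows. Likelihood methods and standard imputation both need MAR, so exchanging them would not help, and the rule is right for continuous outcomes. A reader might also infer that the primary test has an inflated type I error. That needs an adverse assumption. For example, with no effect, if the intervention arm lost 10% of controlled and 40% of uncontrolled subjects and the control arm 20% of each, the false benefit would be 3 to 5 points. With a standard error of √(2·0.55·0.45/163) = 5.5 points, type I error would be about 9% to 15%. The documents give no support for that pattern.

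**Conclusion.** The point holds as an error in what the protocol states about its binary outcomes. The likelihood justification is false for GEE and not assured for the 12-month logistic regression. Standard imputation does not address dropout driven by unobserved variables related to the outcome; the unspecified sensitivity analyses are the only provision for that case and are not tied to a not-MAR method. The word conservative is not justified for the no-change rule.

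The size is conditional on the simulation's assumptions. With dropout linked to control in the intervention arm only, averaging 20% overall, the unadjusted completer odds ratio moves from 1.91 to about 2.25 under MAR, and imputation remains at 2.68 under not-MAR. With the same mechanism in both arms, the completer and imputation odds ratios lie between 1.90 and 1.92. Material bias is therefore possible, not expected.

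**What to change.** In section 7:

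1. **Missing data, MAR.** Limit the likelihood statement to the linear mixed model. For 12-month ACT control, use multiple imputation by arm from baseline ACT, 6-month ACT and baseline predictors of dropout, or a likelihood-based random-effects logistic model.
2. **Missing data, not MAR.** Drop the reliance on plain PROC MI and the assurance that goes with it. Define the promised sensitivity analyses as delta-adjusted imputation or a tipping-point analysis, by arm.
3. **Differential dropout and attrition.** Delete the claim that the no-change assumption is conservative and keep that analysis as supplementary.

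The cost is revised wording and some extra analysis work. No new data are needed, since baseline and 6-month ACT are already collected, and the sample size of 408 is unchanged. The downside is that the primary estimate will depend on an imputation model (or on the random-effects model), which has to be specified in advance.
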